##### Reward Processing

Reward processing will be measured using the Reward Probability Index (RPI; Carvalho et al., 2011) and the Temporal Experience of Pleasure Scale (TEPS; Gard et al., 2006). The RPI is a 20-item self-report instrument that measures the presence of environmental reward, while the TEPS is an 18-item self-report instrument that measures the ability to experience pleasure. Reliability (RPI: α = .93, TEPS: α = .75) and discriminant and convergent validity have been supported for both instruments (for example: the RPI was related to another measures of reward, but not to measures of anxiety and support, and was related to experiencing rewarding behavior; the TEPS was relatable but also distinguishable from other measures of motivation and pleasure; Carvalho et al., 2011; Gard et al., 2006; Simon et al., 2018). An example item of the RPI is: ‘I have many interests that bring me pleasure.’ (RPI). An example item of the TEPS is: ‘I enjoy taking a deep breath of fresh air when I walk outside’.

#### Secondary Outcome: Psychological Symptoms

##### Depression

Depression will be measured with the Beck Depression Inventory-II (BDI-II; Beck et al., 1996). The BDI-II is a 21-item self-report instrument assessing depressive symptoms during the last two weeks. The items are rated from 0 to 3, higher scores representing more symptom severity. A score 0–13 indicates minimal depression, 14–19 mild depression, 20–28 moderate depression and 29–63 severe depression. Reliability and validity have been supported (i.e., test retest reliability between .73-.96, α = .85, convergent and discriminant validity; Beck et al., 1988; Wang & Gorenstein, 2013). For the purpose of this study, the BDI-II will be adjusted to assess depressive symptoms during the past week.

##### General Psychological Distress

Additional psychological symptoms will be measured using the Brief Symptom Inventory (BSI; (Derogatis & Melisaratos, 1983). The BSI consist of 53 items rated on a 0 (not at all) to 4 (extremely) scale and includes the following subscales: somatization, obsessives-compulsive, interpersonal sensitivity, depression, anxiety, hostility, phobic anxiety, paranoid ideation and psychoticism. Reliability and validity of the scale have been supported (i.e., Cronbach’s alpha of .85, concurrent and divergent validity was supported; de Beurs & Zitman, 2006; Geisheim et al., 2002).

#### Potential Moderators: Learning Capacity

##### Memory Functioning: Verbal Working Memory

Verbal working memory will be measured using the N-back task (Braver et al., 1997). The n-back task measures verbal working memory. During the n-back task participants will be asked if a letter on the screen matches a letter previously (1-back, 2- back, 3-back) presented for 500 ms with an interval of 2000 ms. WM load increases as the task progresses from 1-back to 3-back. Accuracy of responses (total of correct hits (% correctly identified *n*-backs) and correct no hits (% correctly identified no presence of a *n*-back)) are measured and will be used as an outcome measure. The *n*-back task has been considered as a valid measure of working memory (Cronbach’s alpha = .92; Schmiedek et al., 2014; Wilhelm et al., 2013).

##### Memory Functioning: Visual Working Memory

Visual working memory will be measured using the probe change detection task (PCDT; Dai et al., 2019). The PCDT consists of the following steps: 1. Participants are instructed by an arrow on their screen to focus on the left or right side of the screen (200 ms), 2. After a short break (300 ms) the screen is filled with colored squares on a gray background (100 ms). The squares are equally distributed between the left and right side of the screen. Participants are instructed to remember only the squares on the side that was instructed under Step 1, 3. After a second blank screen (900 ms), participants see again a field with colored squares (750 ms) and have to indicate whether the squares on the side of the screen are the same as under Step 2. Set sizes of the trial different between 8 to 12 colored squares in total. Participants will receive a total of 300 trials. Reliability and validity has been supported (i.e., test retest reliability between .52-.75; Dai et al., 2019).

##### Memory Functioning: Long-Term Memory

Long-term memory will be measured using the paired associates task (PAT; Unsworth et al., 2009). Long-term memory can also be considered as 'secondary memory', i.e., the part of memory where information is stored when the primary memory, where new information is temporary maintained is full. During the PAT, participants will be given three lists of 10 non-semantically related word pairs. All words are common nouns, and the word pairs will be presented vertically for 2 sec each. Participants will be told that the cue would always be the word on top and that the target would be on bottom. After the presentation of the last word (which takes 20 seconds), participants will see the cue word and "???" in place of the target word. Participants will be instructed to type in the target word from the current list that matches the cue. Cues will be randomly mixed so that the corresponding target words are not recalled in the same order as that in which they had been presented (i.e., this means that the time between encoding and recall varies and lies between the 2 and 70 seconds). Participants will have 5 sec to type in the corresponding word. A participant’s score is the proportion of items recalled correctly. Words will be taken from the Toronto Word Pool (Friendly et al., 1982). The paired associates task has been considered a valid task of long-term memory (Unsworth et al., 2009; Wilhelm et al., 2013).

##### Emotional Bias: Sustained Selective Attention to Emotional Stimuli

Selective attention will be measured using a free-viewing eye-tracking task (Klawohn et al., 2020). Participants will view two blocks of neutral and happy and neutral and sad faces in counterbalanced order while their gaze patterns are concurrently recorded as index of selective spatial attention. Each block will take 30 trials that last 6 seconds. Each trial will show 16 different faces and participants will be asked to freely view the trials. Participants’ gaze location and duration will be assessed using Eyelink eye-tracker software (https://www.sr-research.com/). The present study will use the exact same task as was recently used and validated by Klawohn and colleagues (2020). To maximize reliability of the task (MacLeod et al., 2019), it will be completed twice at baseline. To further investigate the predictive value of the task, an additional post procedure measurement (i.e., at one week follow-up) will be completed.

#### Other Measures

##### Recall

Patient recall will be measured using the Patient Recall Test (PRT; Lee & Harvey, 2015). The PRT measures recall of the previous session content. Following procedures of Lee & Harvey, the patient will be given 10 minutes to remember as much treatment points from the previous session as possible (past session recall). In addition, cumulative recall (i.e., what is remembered from all sessions) will be measured at the follow-up session. Treatment points will be defined as remembering insights, skills and strategies of the CBT model. Scores will be rated by two independent raters, inconsistencies in scoring will be resolved by discussion. Interrater reliability between raters will be computed. The PRT showed good interrater reliability in previous studies (ICC = .92; Dong, Zhao, et al., 2017). In addition to recall of the patient, therapists are also asked to give a rating of recall on a 1-10 VAS scale (1 = patient has no memory of the previous session, 10 = patient remembers everything perfectly).

##### Manipulation Check

To check if patients in the CBT skill acquisition + mental imagery condition engaged in vivid mental imagery, they will be asked to note how vivid the imagery of the skills practiced in this session was on a scale from 1 (not vivid at all) to 10 (extremely vivid). To check and potentially control for self-efficacy, motivation and anticipated reward in the analyses, participants in all conditions will complete questions on a 0-10 scale and asked to rate based on today's session how capable they feel in coping with their dysfunctional beliefs and behaviors, their motivation to use the content of today's session to do something different in the upcoming week and their anticipated reward of doing something different in the upcoming week based on today's session. In addition, expected success of the SKILT study sessions in reducing depressive symptoms will be asked at baseline and after the first session. At the end of the study, patients will be asked to rate on a 0-10 scale to what degree the received sessions contributed to an improvement in depressive symptoms.

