### Randomization and Procedure

Patient who are eligible to participate in the study will complete a baseline measurement and an introduction session on different days. The baseline measurement will take place in the lab and includes a measurement of learning capacity. Informed consent will be signed before the baseline measurement. The order of the measurements during the baseline measurement will be randomized for each participant in order to control for potential fatigue effects. The introduction session is conducted by the therapist and focuses on introducing the principles of CBT and completing the Core Belief Interview (CBI; McBride et al., 2007). After the introduction session, patients will be randomized into one of the three conditions ﻿using a computer script performing block randomization (1:1:1, block size = 15). Block randomization will be done by a researcher who is not involved in the study measurements. Randomization will be pre-stratified on severity of depression (mild [Beck Depression Inventory-II (BDI-II) = 14-19] vs. moderate to severe [BDI-II ≥ 20]). Therapy sessions will be completed weekly and the total study procedure from baseline measurement to the post measurement will take a maximum of 5 weeks. The researchers who perform the study measurements are blind for the therapeutic procedures. The full study procedure is also presented in Figure 2. Participants do not receive financial incentives for participation in this study.

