### Therapeutic Procedures

All therapeutic procedures use techniques from the protocol for cognitive behavioral therapy (CBT; Beck et al., 1979) for depression and use agenda setting to structure the sessions. In addition, each procedure will focus on targeting the idiosyncratic beliefs and behaviors that were established during the CBI. However, the procedures differ in the number of active ingredients (see Figure 3 and data supplement 1). During the active control procedure, the therapist and patient will focus on discussion of dysfunctional thoughts and behaviors only. Therapists in this condition will be explicitly instructed to focus purely on exploring the relation between dysfunctional thinking and behavior and depressive symptoms, and not to engage in evaluating dysfunctional thinking or behavioral activation. During the CBT skill acquisition procedure (CBTSAP), the therapist and patient will choose one of the cognitive or behavioral skills from a predefined list of CBT skills (i.e., consisting of behavioral activation (behavioral therapy skill) and questions used for evaluating dysfunctional thoughts (cognitive therapy skill). Subsequently, the therapist and patient will discuss how this skill could be or have been applied in past or future situations in which idiosyncratic beliefs and behaviors may (have) lead to negative mood. During the CBTSAP plus mental imagery, the therapist and patient will not only discuss application of the skill but in addition, engage in a mental imagery exercise of skill application. The mental imagery exercise is based on a guided mental imagery procedure and has been shown to increase motivation for goal directed behaviors (Heise et al., 2022; Renner et al., 2019). During the mental imagery procedure, participants are instructed to imagine as vividly as possible and focusing on the positive aspects of the image. The procedure consists of the following steps: 1) imagine the contextual cues (e.g., place, date) of a future or past situation with depressive symptom(s), 2) engaging in multi-sensory imagery of applying the CBT skill in this situation, 3) imaging and experiencing the positive aspects related to successfully applying the CBT skill. All sessions will be videotaped for treatment fidelity checks. Research intervision will take place regularly. The agenda for each therapeutic procedure and the list of CBT skills that can be chosen from and practiced in the CBTSAP procedures is given in data supplement 1 and 2.

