### Instruments

An overview of all patient measurements is given in Table 1. An overview of all measurements completed by the therapists or third observers can be found in Table 2.

**Table 1 t1:** Overview of Patient Instruments per Time Point

Measurement instruments	Baseline	Introduction session	Session 1	Session 2	Session 3	One day after Session 3	Follow-up
Primary outcomes: therapy processes							
*CBT skills*							
Ways of Responding (WOR)	X						X
Behavioral Activation for Depression Scale – short form (BADS-SF)	X	X	X	X	X		X
Cognitive Change Sustained Change (CCSC)	X	X	X	X	X		X
*Idiosyncratic thoughts and behaviors*							
Core Belief Interview (CBI)		X	X	X	X	X	X
*Dysfunctional thinking*							
Cognition Checklist (CCL)	X					X	X
*Reward processing*							
Reward Probability Index (RPI)	X					X	X
Temporal Experience of Pleasure (TEPS)	X					X	X
Secondary outcomes: symptoms							
*Depression*							
Beck Depression Inventory II (BDI-II)	X	X	X	X	X		X
*Symptoms other than depression*							
Brief Symptom Inventory (BSI)	X						X
Potential moderators: Learning capacity							
*Memory functioning*							
Verbal working memory: n-back task	X						
Visual working memory: Single probe detection task	X						
Long-term memory Paired-associates task	X						
*Emotional bias*							
Free viewing eye-tracking task	X	X				X	
Other measures							
*Recall*							
Patient Recall Test (PRT)			X	X	X	X	X
*Diagnostics*							
SCID-5-CV	X						
** *Demographics* **	X						
** *Treatment evaluation* **							X
** *Manipulation check* **			X	X	X		
** *Procedure check* **							X
** *Expected success* **	X		X				

*Note.* CBTSAP = CBT Skill Acquisition Procedure; MI = Mental Imagery; Structural Clinical Interview for DSM-V Clinical Version (SCID-5-CV).

**Table 2 t2:** Overview of Therapist/Observer Instruments per Time Point

Measurement instruments	Baseline	Introduction session	Session 1	Session 2	Session 3	Post-procedure	Follow-up
Therapy processes							
Therapist-rated recall			X	X	X		
Manipulation check							
Therapy integrity							X
Protocol deviations			X	X	X		

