#### Main Analyses

The main analyses will be conducted in Stata. First, to test the direct effects of the different procedures on change in therapy processes and symptoms, differences on the primary and secondary outcomes between conditions (CBTSAP versus active control; CBTSAP versus CBTSAP + mental imagery; active control versus CBTSAP + mental imagery) will be tested using multilevel analysis with maximum likelihood estimation (measurements [Level 1] nested within patients [Level 2] nested within therapists [Level 3]). Because the WOR is only measured at two time points, differences between conditions on the WOR will be tested using a repeated measures ANOVA.

Second, to test whether the effect of the procedures is moderated by individual differences in learning capacity, learning capacity will be added as a moderator in the model. Moderation will be tested by adding learning capacity as a main factor and the interaction between learning capacity and condition to the multilevel regression model. For the WOR, the interaction will be added to the repeated measures ANOVA. Moderation of learning capacity will be tested separately for memory functioning and emotional bias. Memory functioning will be tested separately for each component of memory functioning (i.e., verbal working memory, visual working memory, long-term memory), while controlling for type I error (*p* < .016).

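### The protocol leaves open, without scope, controlling for self-efficacy, motivation and anticipated reward rated after randomisation; used in a condition comparison, this would no longer estimate the total effect of the procedure

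*Protocol article*

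**What the plan says.** All places are in the protocol article.

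- **Manipulation Check** gives the purpose of three 0-10 ratings collected in every condition: "To check and potentially control for self-efficacy, motivation and anticipated reward in the analyses". For self-efficacy, patients are to "rate based on today's session how capable they feel in coping with their dysfunctional beliefs and behaviors". The motivation item asks about "their motivation to use the content of today's session to do something different in the upcoming week". The item on anticipated reward is likewise tied to the session of that day.
- **Instruments, Table 1**: the row "Manipulation check" is marked at Sessions 1, 2 and 3. Baseline and the introduction session are not marked.
- **Randomization and Procedure**: "After the introduction session, patients will be randomized into one of the three conditions".
- **Therapeutic Procedures**: the guided imagery exercise "has been shown to increase motivation for goal directed behaviors".
- **Main Analyses**: the multilevel model is there "to test the direct effects of the different procedures on change in therapy processes and symptoms". Apart from learning capacity as a moderator, no covariate is named. The Ways of Responding test is analysed by repeated measures ANOVA, again without these ratings.
- **Mediation Analyses**: the listed mediators are the therapy processes and session recall. The three ratings are not among them.

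**The concern.** The ratings are answers to the session just received, and which session that was depends on the arm. A variable that the randomised procedure can change is not a baseline covariate. Conditioning on it in a comparison of arms does two things. It removes whatever part of the effect passes through the rating. It also links arm to any unmeasured cause shared by the rating and the outcome, a link that randomisation had excluded.

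This matters because the trial sets out to isolate one procedure and estimate what it causes. If imagery works partly by raising motivation, adjustment for motivation would hide that part in the contrasts that involve the imagery arm. The clause gives no trigger and does not say which analyses or which session's rating it means, so the choice could be made after the data are seen.

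**Working it through.** **Timing.** Baseline measurement, then introduction session, then randomisation, then Sessions 1 to 3 with the ratings. No rating exists before randomisation, so a pre-treatment version cannot be used instead.

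**Does arm move the ratings?** The protocol says so for motivation under imagery. For self-efficacy and anticipated reward it is plausible from the session content but not stated.

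**Size.** The protocol gives no figure on this point, so there is none to reproduce. Every path value below is an assumption. Let T be arm (0 or 1), M the rating, U an unmeasured common cause with variance 1, and Y the outcome in SD units:

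- M = aT + uU + error, with variance V within arm
- Y = dT + bM + cU + error

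Here d is the part of the effect that does not pass through the rating. Then:

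- arm coefficient without M: d + ab (the total effect, set to 0.50 throughout)
- arm coefficient with M as covariate: d − a·u·c / V

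| a | b | u, c | V | d = 0.50 − ab | Adjusted estimate |
|---|---|---|---|---|---|
| 0 | any | any | any | 0.50 | 0.50 |
| 0.3 | 0.3 | 0, 0 | 1 | 0.41 | 0.41 |
| 0.3 | 0.3 | 0.4, 0.4 | 1 | 0.41 | 0.41 − 0.048 = 0.36 |
| 0.5 | 0 | 0.4, 0.4 | 1 | 0.50 | 0.50 − 0.08 = 0.42 |
| 0.5 | 0.5 | 0, 0 | 1 | 0.25 | 0.25 |
| 0.5 | 0.5 | 0.4, 0.4 | 1 | 0.25 | 0.25 − 0.08 = 0.17 |
| 0.5 | 0.5 | 0.5, 0.5 | 1.25 | 0.25 | 0.25 − 0.10 = 0.15 |
| 0.5 | 0.5 | 0.5, −0.5 | 1.25 | 0.25 | 0.25 + 0.10 = 0.35 |
| 0.5 | 0 | 0.4, −0.4 | 1 | 0.50 | 0.50 + 0.08 = 0.58 |

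A simulation with 200,000 patients per scenario agrees with the formula for the rows with V = 1 and c not negative (for example 0.363, 0.418, 0.252 and 0.169).

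Three things follow.

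- Where arm moves the rating and the paths are positive, these scenarios give about 0.15 to 0.42 in place of 0.50. That is an illustration, not a bound: with V = 1 in place of 1.25, the 0.15 row becomes 0.25 − 0.125 = 0.125, and weaker paths bring the result closer to 0.50.
- The fourth row has no mediation at all, and the estimate still moves.
- The last two rows show that a common cause acting with opposite sign pushes the estimate up, above d or even above the total effect.

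**The case against.** The strongest reply is that no specified analysis contains the adjustment. The clause sits in an instrument description and is worded as a possibility; Main Analyses sets out the model without it, and all analyses are declared intention-to-treat. This stands. A reader might infer that the planned main estimate is already biased, and the documents do not support that.

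A second reply is that the control may be meant for a supplementary or mechanism analysis, where post-randomisation variables are modelled on purpose, and that such lists usually belong in a statistical analysis plan. The first half is possible, but the sentence speaks of the analyses in general and the mediation section does not list these ratings. The second half does not meet the point, which concerns an option that this document states and leaves unbounded, not a detail it omits.

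A third reply is that the statement about imagery carries limited weight. It concerns one of three ratings and only contrasts with the imagery arm, and it supports the link from arm to rating but not the link from rating to outcome. This also stands.

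Finally, the aim of testing direct effects might seem to justify holding the ratings constant. In this protocol the phrase refers to the effect of an isolated procedure. With unmeasured common causes, adjustment would not yield a clean mediator-adjusted effect either.

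**Conclusion.** The point holds as a clarification. The protocol keeps open, without scope, control for three ratings that exist only after randomisation and are tied to the randomised session. Used in a comparison of conditions, that control would replace the total effect with a quantity that the trial does not set out to estimate.

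The timing is certain from the documents. That arm changes a rating is stated only for motivation under imagery. Bias requires that arm does move the rating; if it does not, the estimate is unchanged. Size and direction rest on assumed paths. A reader might go further and conclude that adjustment would wipe out the effect, or must push the estimate below the part that does not pass through the rating. Both depend on chosen path strengths and signs, and nothing in the protocol fixes these.

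**What to change.** In Manipulation Check, remove the option to control for the ratings as far as it applies to the condition comparisons. In Main Analyses, add a sentence stating that the primary and secondary comparisons of conditions adjust for no rating taken after randomisation. Report the three ratings by arm as manipulation checks. Any other use should be in a mediation or sensitivity analysis labelled exploratory, with its assumptions given. Expected success at baseline is collected before randomisation and may serve as a covariate; the protocol does not propose adjusting for its second rating at Session 1, and the same sentence would exclude it from these comparisons.

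The cost is a sentence or two. No measurement, visit or sample size changes.
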